**Figure 2 fig2:**
[figure not shown]
Effect of wearing the elbow forearm support orthosis (**a, b**: front view **b**. side view).

Both groups will begin device usage under the guidance of trained therapists, with daily wearing time of 6 h, distributed as 2 h each in the morning, afternoon, and evening, for a duration of 4 weeks. Therapists will perform weekly device inspections and adjustments according to a standardized protocol. Inspection items include skin integrity (presence of pressure marks, abrasions, or erythema), device positioning, belt tightness, forearm support alignment, elbow joint angle, and patient-reported comfort and pain levels (assessed using the Visual Analog Scale). Any deviation from the predefined criteria necessitates immediate adjustment and patient re-education.

During the study period, the use of other shoulder joint orthoses or fixation devices is strictly prohibited, as are invasive treatments such as botulinum toxin injections and intra-articular injections, as well as therapeutic modalities that may affect shoulder joint muscle tone, including transcranial magnetic stimulation and electrical stimulation. Additionally, patients are not permitted to participate in other clinical research projects.

### Outcome measures

The primary outcome measures of this study are the VD and HD from the inferior margin of the acromion to the center of the humeral head. These measurements will be obtained through standardized X-ray examinations. During examination, patients will adopt a standard sitting position with both upper limbs naturally hanging down and shoulders in neutral position. The X-ray tube center will be aligned at the height of the superior edge of the lateral end of the clavicle, horizontally positioned in line with the midline of the humeral head, angled 15° caudally, and positioned 1 meter from the patient. All imaging examinations will be performed by trained radiologic technicians, and image measurements will be independently completed by two senior radiologists blinded to group allocation. If the measurement difference between the two assessors exceeds 1 mm, a third senior radiologist will make the final determination.

Secondary outcome measures include: Modified Ashworth Scale (MAS) scores to assess the degree of spasticity in shoulder adductor and elbow flexor muscle groups (14); Visual Analog Scale (VAS) scores to evaluate shoulder pain intensity (15); Fugl-Meyer Assessment for Upper Extremity (FMA-UE) to assess upper limb motor function recovery (16); Modified Barthel Index (MBI) to evaluate activities of daily living, with particular attention to upper limb-related items (17).

Rationale for Outcome Measures Hierarchy: Our outcome selection reflects the theorized causal sequence of the intervention. Primary outcomes (VD/HD) directly quantify the device’s most immediate mechanical effect—humeral head repositioning. These measures are the most objective, least subject to confounding, and directly test the biomechanical hypothesis. Secondary outcomes are positioned at subsequent stages of the causal pathway: (a) MAS and VAS measure the neuromuscular benefits of improved alignment (reduced tone and pain); (b) FMA and MBI capture the functional consequences of improved motor control and reduced pain, which should emerge as downstream benefits. This staged framework ensures that outcome assessment timepoints are selected based on mechanistic expectations rather than statistical convenience.

### Predetermined visit schedule

All assessment measures will be obtained at baseline (0 weeks), 4 weeks of treatment, 8 weeks of treatment (4 weeks follow-up), and 12 weeks of treatment (8 weeks follow-up). Primary outcome X-ray examinations will be conducted in the hospital radiology department, while secondary outcome assessments will be completed at the rehabilitation medicine assessment center. Raw data from each assessment will be independently entered into electronic case report forms (REDCap system) by two research assistants and cross-verified. If patients are unable to attend scheduled assessments, home visits will be arranged. All follow-up data will be promptly recorded in standardized follow-up forms. The visit schedule for all assessments is presented in Table 1.

### Quality control, data collection, and safety measures

To ensure research quality, all therapists participating in the study must complete standardized training and pass assessments. To ensure protocol fidelity and detect potential performance bias: all therapists will complete standardized training covering rehabilitation content, progression algorithms, and technique consistency prior to study initiation; a detailed treatment log will be completed by therapists for each session, documenting specific exercises administered, number of repetitions, patient tolerance/pain level, and modifications; monthly fidelity audits will be conducted on a random 20% sample of treatment sessions, with blinded evaluation against standardized checklists; and treatment adherence rates will be calculated and reported by group to assess for differential treatment intensity. Patients will be required to maintain rehabilitation diaries recording daily device usage. During the home rehabilitation period, they will also record rehabilitation activity content, activity duration, and wearing time. The research team will assess patient compliance during each outcome evaluation.

This study employs the Research Electronic Data Capture (REDCap) cloud platform for data management. All data collection forms are structurally designed with built-in logic checking functions.

Potential adverse events in this study include: pressure-related skin injuries, local discomfort, and worsening shoulder pain. All adverse events will be reported in real-time through the REDCap system, and serious adverse events must be reported to the Ethics Committee within 24 h.

### Statistical analysis

This study will employ intention-to-treat (ITT) analysis as the primary analytical approach, with per-protocol (PP) analysis conducted as a sensitivity analysis. The ITT analysis set includes all randomized participants, while the PP analysis set includes participants who completed the full 12-week follow-up with device usage compliance ≥80%. All statistical analyses will be performed using R software version 4.2.0, with significance level set at *α* = 0.05 (two-sided test).

For baseline characteristics analysis, continuous variables will be presented as mean ± standard deviation or median (interquartile range) according to their distribution characteristics, and categorical variables will be presented as frequency (percentage). Between-group baseline comparisons will employ independent samples t-test or Mann–Whitney U test (for continuous variables), and chi-square test or Fisher’s exact test (for categorical variables).

Analysis of primary outcome measures (VD and HD) will employ mixed-effects linear models to account for the correlation of repeated measurements. The model will include fixed effects (treatment group, time point, and their interaction) and random effects (participant), with adjustment for baseline values and pre-specified covariates. Between-group differences will be expressed as least squares mean differences estimated from the model with their 95% confidence intervals.

Secondary outcome measures will be analyzed using different statistical methods. For ordinal categorical variables such as MAS scores and VAS scores, generalized estimating equations (GEE) models with cumulative logit link functions will be used. For continuous variables such as FMA-UE and MBI scores, the same mixed-effects model approach as the primary outcomes will be employed. Secondary outcome comparisons will be adjusted for multiple testing. For the primary analysis, we will apply Bonferroni correction to control family-wise.

error rate across secondary outcomes. However, given the expected correlation among secondary outcomes (pain, motor function, spasticity)—which may render Bonferroni overly conservative—we will additionally report results using the Holm-Bonferroni procedure (which maintains family-wise error control with less conservatism) and examine false discovery rate for comparative interpretation. Subgroup and sensitivity analyses are designated as exploratory given sample size limitations. Missing data will be handled using multiple imputation based on Markov Chain Monte Carlo (MCMC) methodology. The imputation model includes all baseline covariates (age, time since stroke, baseline GHS severity, stratification factors) and time-varying measurements of primary and secondary outcomes at available timepoints. We assume missing data are missing at random (MAR).

conditional on observed covariates—a reasonable assumption given that dropout is primarily due to logistical constraints (missed appointments) rather than outcome-dependent missingness. Twenty complete datasets will be generated, analyzed separately, and results combined using Rubin’s rules. Sensitivity analyses will assess robustness to departure from the MAR assumption.

This study will also conduct pre-specified subgroup analyses, including stratification by stroke type, baseline degree of GHS, and time from onset to enrollment. These analyses will assess heterogeneity of treatment effects by adding interaction terms between subgroup variables and treatment modality to the primary analysis models. Given sample size limitations, subgroup analysis results will be interpreted as exploratory analyses. To evaluate the robustness of results, a series of sensitivity analyses will be performed, including comparisons of different analysis sets, alternative missing data handling methods, and different statistical models.

The complete statistical analysis plan will be finalized and archived before enrollment of the first patient. The analytical process will be executed by an independent statistician who does not participate in study implementation and data collection.

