This study comprises two parallel groups: the intervention group (elbow-forearm support orthosis) and the control group (conventional shoulder sling). During the 4-week intervention period, patients in both groups will use their respective devices regularly for 6 h daily while simultaneously receiving standard rehabilitation therapy according to current clinical guidelines. To ensure standardized intervention implementation, all healthcare personnel involved in treatment will receive systematic training in device usage and monitoring protocols. Following the completion of the 4-week intervention, an 8-week follow-up period will be conducted, during which patients will maintain daily rehabilitation diaries.

This study has established a rigorous quality control system to ensure data quality and trial integrity. All research procedures will be strictly executed according to standard operating procedures, with independent clinical research assistants conducting regular monitoring visits to verify protocol compliance and data accuracy. Trial data will be collected through electronic case report forms within the REDCap system, which incorporates built-in data range checks and validation rules to effectively ensure data quality. Additionally, a comprehensive adverse event recording and assessment mechanism has been established.

Outcome measure assessments will be conducted at baseline, and at 4, 8, and 12 weeks post-randomization. Primary outcome measures will employ standardized imaging techniques to measure VD and HD from the inferior margin of the acromion to the center of the humeral head. All imaging measurements will be performed by independent radiologists who are blinded to group allocation, ensuring objectivity and reliability of assessment results.

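### Two unranked primary outcomes, three visits, one alpha of 0.05: with no deciding visit and no either/both rule, nothing in the plan holds the primary error rate at 5%

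*Protocol article*

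**What the plan says.** All references are to the Protocol article.

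- **Outcome measures** gives two primary outcomes without ranking them: "The primary outcome measures of this study are the VD and HD from the inferior margin of the acromion to the center of the humeral" (sentence cut short here).
- **Study design and methods** sets three post-baseline visits: "Outcome measure assessments will be conducted at baseline, and at 4, 8, and 12 weeks post-randomization". Table 1 marks VD and HD at each of them.
- **Statistical analysis** names the same method for both outcomes: "Analysis of primary outcome measures (VD and HD) will employ mixed-effects linear models to account for the correlation of repeated measurements". It sets one level for all analyses, "with significance level set at *α* = 0.05 (two-sided test", and one model form: "The model will include fixed effects (treatment group, time point, and their interaction) and random effects (participant"). Results are reported as follows: "Between-group differences will be expressed as least squares mean differences estimated from the model with their 95% confidence intervals". No visit is attached to these differences.
- **Statistical analysis**, on multiplicity: "Secondary outcome comparisons will be adjusted for multiple testing". Bonferroni is the main method, with Holm and the false discovery rate reported alongside. The Bonferroni sentence opens by referring to the primary analysis, but the family it covers is the secondary outcomes.
- **Sample size calculation** uses an endpoint-only t-test on VD at the full two-sided 0.05 with power 0.80. It arrives at 25 per group, raised to 30 for 20% dropout. The week of that endpoint is not named.

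**The concern.** Three choices that define the primary hypothesis are left open: which outcome decides, at which visit, and whether one success is enough or two are needed. The article does fix the level (0.05 everywhere) and the scope of multiplicity control (secondary outcomes). A secondary claim is thus held to a stricter standard than a primary one.

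Two things are at stake. If either outcome, or any visit, may carry the claim, the chance of a false positive primary result exceeds the stated 5%. If both must succeed, the error rate is safe, but the sample size was set for one outcome and its power does not carry over to the pair. While the rule is unstated, the deciding contrast could be picked after the results are known.

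**Working it through.** **Inputs from the article.** Two primary outcomes; three post-baseline visits; two-sided alpha 0.05; VD difference 5.2 mm with SD 6.8 mm; HD difference 4.8 mm with SD 6.2 mm; power 0.80; 25 per group, 30 after dropout. With 20% loss, 30 × 0.80 = 24 per group remain.

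**Inputs assumed.** Correlation between visits 0.5–0.85 and between VD and HD 0–0.7. The article gives neither, so a wider range is shown as well.

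**1. The plan's own figure.** By the normal approximation, n = 2(1.960 + 0.842)² × (6.8/5.2)² = 26.8, so 27 per group for VD. The t-test that the article names needs 28. HD also gives 27 and 28. The stated 25 is slightly below both. That is a separate matter, but it affects the power figures in step 6: VD has 75.5% power at 25 per group and 73.7% at 24. The article states no family-wise error for the primary outcomes, so there is none to reproduce.

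**2. Reference values under independence**, 1 − (1 − 0.05)^k:
- k = 2: 1 − 0.95² = 9.75%
- k = 3: 1 − 0.95³ = 14.3%
- k = 6: 1 − 0.95⁶ = 26.5%

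**3. Either outcome, one contrast each.** P(at least one) = 0.05 + 0.05 − P(both).
- VD–HD correlation 0: 0.10 − 0.0025 = 9.75%
- Correlation 0.5: 0.10 − 0.0092 = 9.1%
- Correlation 0.7: 0.10 − 0.0165 = 8.35%

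This applies to one named visit, and equally to a single overall contrast per outcome.

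**4. Any of six comparisons.** Simulated null z-statistics (2 outcomes × 3 visits, multivariate normal), each tested at |z| > 1.96:

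| Visit correlation | VD–HD correlation | Any of six | One outcome, any of three visits |
|---|---|---|---|
| 0.5 | 0 | 23.4% | 12.5% |
| 0.7 | 0.5 | 19.1% | 10.9% |
| 0.85 | 0.7 | 15% | 9% |
| 0.3 (wider range) | 0 | 25.3% | 13.6% |
| 0.9 (wider range) | 0.8 | 12.7% | 8.4% |

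**5. Both outcomes required at one named visit.** The error cannot exceed 5%. With no effect on either outcome it is 0.25–2.2% for VD–HD correlations of 0–0.8.

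**6. Power if both are required.** Unadjusted t-tests at 24 per group have power 73.7% (VD) and 74.7% (HD). Under independence, 0.737 × 0.747 = 55%. At correlation 0.5 it is 61%, and at 0.7 it is 64%.

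**The case against.** **Six tests are not stated.** A reader might infer that the plan tests each outcome at each visit and lets any one of the six carry the claim, so that the false positive rate simply is 15–23%. The article does not say this. The fixed part, "fixed effects (treatment group, time point, and their interaction"), also fits one overall mean difference per outcome or one interaction test per outcome. What is documented is silence on the rule, so 15–23% is the upper end of the possible readings and rests on assumed correlations. This stands.

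**A both-required rule would be safe on error.** This is true. The sizing section considers VD and HD together and takes VD as the one said to need more patients, which is compatible with requiring both. The article does not state such a rule, however.

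**The 55–64% power should not be charged to the both-required rule alone.** A reader might set it against the stated 80% and put the whole gap down to that rule. But VD alone has only 74% at 24 per group. At 28 per group, where each outcome has about 80%, power for both is about 67–74% (normal approximation). The calculation also ignores the planned baseline adjustment and multiple imputation. If baseline and follow-up correlated at 0.5 (an assumption), power for both at 24 per group would be about 75–80%. The article supports only that power for both is lower than for VD alone.

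**The analysis plan may settle it.** The article says a complete plan is archived before the first enrolment, and contrast details often sit there. That would excuse leaving out test mechanics. It is a weaker excuse here, because the article sets out three multiplicity procedures and restricts them to the secondary outcomes, while the deciding visit and success rule are part of the hypothesis itself.

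**Conclusion.** The concern holds in a conditional form. The article has two unranked primary outcomes, three post-baseline visits, one alpha of 0.05, no deciding visit, no either/both rule, and multiplicity control for secondary outcomes only. Under those rules the primary family-wise error is not held at 5%:

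- **Either outcome on one contrast each:** about 8–10%.
- **Any of six comparisons:** up to about 15–23% under the assumed correlations, and 13–25% over the wider range.
- **Both outcomes required:** no inflation, but lower power than for VD alone (about 55–64% against 74%, unadjusted, 24 per group). Part of the distance to 80% comes from the sizing itself, and the planned model may recover some.

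The gap does not depend on the assumed correlations; only the size of the inflation does. Because the rule cannot credibly be chosen once results are known, it should be settled first.

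**What to change.** Before unblinding, state in the protocol and the analysis plan:

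1. **One primary visit** for the model's least squares mean difference. Week 4, the end of device wear, fits the Outcome measures section, which treats VD and HD as the device's most direct mechanical effect. Week 12 is also defensible if the sponsor justifies it; it would then test whether the effect persists after wear has ended.
2. **A fixed sequence at that visit:** VD at two-sided 0.05, then HD at 0.05 only if VD is significant. This holds the family-wise error at 5% and matches the VD-based sizing.
3. **The other visits as secondary**, within the multiplicity scheme already planned for secondary outcomes.

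If the archived analysis plan already contains such a rule, bringing it into the protocol is enough.

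**Cost.** Wording only, with no extra patients and no loss of power for VD. HD cannot be claimed if VD fails, and the chance of claiming both is the both-significant power shown in the working. For comparison, testing VD and HD at 0.025 each would need 33–34 evaluable per group for 80% power on VD: 33/0.80 = 41.3 and 34/0.80 = 42.5, so 42–43 per group and 84–86 in total. The article leaves enrolment status unclear, so the change should be dated and recorded as made before unblinding.

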## Introduction

Stroke is one of the leading causes of adult disability worldwide, with approximately 13.7 million new cases annually (1). Glenohumeral subluxation (GHS), a common complication following stroke, occurs in up to 73% of patients during the acute phase, with symptoms deteriorating over time in 67% of affected individuals (2). GHS not only reduces proprioception in the affected limb and exacerbates shoulder pain but also significantly restricts shoulder range of motion, ultimately impairing upper limb functional recovery and activities of daily living (3).

Current clinical approaches for managing GHS include functional electrical stimulation (4), kinesiotaping (5), and shoulder orthoses (6). However, meta-analysis results indicate that these conventional therapeutic techniques demonstrate suboptimal efficacy in improving post-stroke GHS (7). Notably, the only intervention recommended by the American Stroke Rehabilitation Guidelines is maintaining comfortable upper limb positioning and using supportive devices, though this recommendation carries a low level of recommendation and evidence quality (Class IIa recommendation; Level C evidence) (8).

Conventional support devices, such as the Harris hemiplegic sling and Bobath sling, while providing some immediate benefits, have significant limitations: these devices tend to slip due to gravitational forces, are prone to displacement during movement, can only achieve vertical reduction without anterior–posterior repositioning, and demonstrate incomplete overall reduction effects (9, 10). To address these challenges, our team has developed an innovative elbow-forearm support orthosis using 3D printing technology (Chinese Patent No.: CN201810839207.6). Preliminary studies demonstrate that this device significantly outperforms traditional traction-type orthoses in terms of immediate reduction effectiveness and user satisfaction (11).

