### Sample size calculation

The sample size calculation for this study is based on the primary outcome measures of VD and HD from the inferior margin of the acromion to the center of the humeral head. According to Kumar et al. (12), the expected difference for VD is 5.2 ± 6.8 mm, and for HD is 4.8 ± 6.2 mm. Since the sample size calculation based on VD difference yields a larger result, we chose to base our sample size estimation on VD.

With a two-sided significance level of *α* = 0.05 and power (1-*β*) = 0.80, we employed the sample size calculation formula for independent samples t-test. Calculations were performed using PASS software (version 15.0, NCSS, LLC., Kaysville, Utah, United States) (13). Based on the systematic review by Nadler et al. (6), similar studies with 6–12 week follow-up periods report dropout rates of 15–25%. Considering that this is a single-center study with a 12-week follow-up period, we adopted a relatively conservative estimate and set the dropout rate at 20%.

Based on these parameters, the minimum required sample size is 25 participants per group. Accounting for a 20% dropout rate, we determined to recruit 30 participants per group, for a total sample size of 60 participants. The recruitment period is anticipated to last 6 months; if the planned sample size is not achieved, the recruitment period will be appropriately extended. We acknowledge that our sample size calculation, while based on the conservative.

endpoint-only t-test approach, will be analyzed using mixed-effects linear models that leverage repeated measures and within-subject correlations. This mismatch is intentional and conservative: mixed models typically provide greater statistical power than endpoint-only comparisons. Thus, our sample size of *N* = 60 represents a conservative estimate and ensures adequate power across analysis approaches.

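### Read literally, the VD/HD mixed model gives every visit contrast one pooled standard error; if visit variances differ, the intervals at weeks 4 and 12 are miscalibrated, so an unstructured covariance should be specified

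*Protocol article*

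**What the plan says.** All references are to the protocol article.

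- **Fixed part (Statistical analysis).** "The model will include fixed effects (treatment group, time point, and their interaction").
- **Random part (same sentence).** "random effects (participant), with adjustment for baseline values and pre-specified covariates". No residual covariance structure is given. Baseline is adjusted for, with no mention of a baseline effect that differs by visit.
- **What is reported (same section).** "Between-group differences will be expressed as least squares mean differences estimated from the model with their 95% confidence intervals". No visit is named as primary.
- **Visits (Study design and methods).** "Outcome measure assessments will be conducted at baseline, and at 4, 8, and 12 weeks post-randomization".
- **Wear period (same section).** "Following the completion of the 4-week intervention, an 8-week follow-up period will be conducted". Table 1 marks the interventions only at baseline and in the treatment column.
- **Variability (Sample size calculation).** "the expected difference for VD is 5.2 ± 6.8 mm, and for HD is 4.8 ± 6.2 mm". This is one SD per outcome, with none by visit and no correlation between visits.

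The Statistical analysis section also applies the VD/HD model to FMA-UE and MBI, and it lists different statistical models among its sensitivity analyses without specifying them.

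**The concern.** A participant random intercept with independent, equal-variance residuals is a compound-symmetry model. It has one variance for all visits and one correlation for all pairs of visits. Every group-by-visit contrast then has the same standard error, whatever the true spread at that visit.

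This design gives reason to doubt that the visits are exchangeable. Week 4 closes the wear period, while weeks 8 and 12 fall four and eight weeks after it. Adjusting for baseline adds a second reason. If correlation with baseline weakens with time, the variance left after adjustment grows from week 4 to week 12 even when the raw SD stays constant.

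The calibration of the visit-specific intervals is at stake. A visit with below-average residual variance gets an interval that is too wide and loses power. A visit with above-average residual variance gets one that is too narrow, and its type I error exceeds 5%.

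**Working it through.** **Figure to reproduce.** None: the article states no interval width, visit-specific SD or correlation. The correlations below are assumptions. The SD of 6.8 mm for VD comes from the Sample size calculation and cancels out of the ratios.

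**Step 1, formula.** With complete balanced data, the random-intercept standard error is governed by the mean of the visit-specific residual variances v(t). Hence

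model SE / true SE at visit t = k(t) = sqrt( mean of v / v(t) ),

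and the type I error of a nominal 5% test is about 2 × [1 − Φ(1.96 × k(t))].

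**Step 2, residual variances with equal SD and decaying correlation.** Let r be the correlation with the baseline value. Under AR(1) with correlation ρ per 4 weeks, r = ρ, ρ², ρ³ at weeks 4, 8 and 12. In units of the raw variance, v(t) = 1 − r(t)².

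- ρ = 0.6: r = 0.6, 0.36, 0.216; v = 0.640, 0.870, 0.953; mean 0.821.
- ρ = 0.8: r = 0.8, 0.64, 0.512; v = 0.360, 0.590, 0.738; mean 0.563.

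| ρ | k, week 4 | k, week 8 | k, week 12 | Type I error, week 4 | Type I error, week 12 |
|---|---|---|---|---|---|
| 0.6 | 1.13 | 0.97 | 0.93 | 2.6% | 6.9% |
| 0.8 | 1.25 | 0.98 | 0.87 | 1.4% | 8.7% |

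**Step 3, one baseline slope for all visits.** The article mentions no baseline-by-visit term. With a common slope b = mean of r, v(t) = 1 − 2·b·r(t) + b².

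- ρ = 0.6: b = 0.392; v = 0.683, 0.871, 0.984; k = 1.11 and 0.93; type I error 2.9% (week 4) and 6.9% (week 12).
- ρ = 0.8: b = 0.651; v = 0.382, 0.590, 0.757; k = 1.23 and 0.87; type I error 1.6% and 8.7%.

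**Step 4, simulation under no effect.** With 25 per arm, complete data and SD 6.8, the random-intercept model gave about 3.2% (week 4) and 6.4% (week 12) at ρ = 0.6, and about 1.5% and 8.8% at ρ = 0.8. At ρ = 0.8, visit-specific variances gave about 5% at every visit. The formulas agree with these to within about 0.6 percentage points. A separate run of 300 replicates at ρ = 0.8 shows the cause. The model SE was 1.46 mm at all three visits, while the estimates had empirical SDs of 1.24, 1.37 and 1.64 mm.

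**Step 5, cases that go the other way.**

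- Equal SD and equal correlation: v is the same at every visit, so k = 1 throughout. In simulation with correlation 0.7, the SE was 1.38 mm with either model.
- Residual SD falling from 1.5 to 1.25 to 1: v = 2.25, 1.5625, 1; mean 1.604; k = 0.84 at week 4 and 1.27 at week 12. The direction reverses.
- Equal correlation 0.7 with the SD falling by 30% by week 12 (300 replicates): model SE 1.19 mm against empirical 1.40, 1.18 and 0.93 mm; coverage 90.3%, 95.3% and 97.7%.

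**Step 6, average over visits.** The variance of this contrast depends on the variance of the participant means. The random-intercept fit estimates that directly from the data, so pooling across visits does little harm.

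**The case against.** **The text does not say that the participant effect stands alone.** A random participant effect can be combined with a structured or unequal-variance residual, and such details are often left to an analysis plan. The article refers to a complete one that is not shown. This stands: it cannot be said that the plan forces compound symmetry. But the article does set out the primary model term by term, and the model as written is the random intercept. Proposing a better model for a stated choice is different from complaining of a missing detail.

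**The direction is not established.** A reader might infer that the week-4 interval will be too wide and the week-12 interval too narrow. The article does not support that as a fact, because it has no visit-specific SDs or correlations. The Introduction does describe GHS "with symptoms deteriorating over time in 67% of affected individuals". That concerns symptoms in a background population, and a worsening average does not imply a growing spread of radiographic distances in treated participants. Decaying correlation is plausible, but it remains an assumption.

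**No visit is designated.** A reader might also infer that the trial's main test has an inflated error rate. That would need a designated week-12 test, and none is named. Visit contrasts are a natural product of the interaction term, so the point applies to them and hardly at all to an average over visits.

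**Sensitivity analyses with other models are planned.** They are unspecified and would not correct the primary intervals.

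**Conclusion.** The point holds in conditional form. If the model is fitted as written, with a random intercept and default residuals, the visit-specific VD and HD intervals share one pooled standard error and are correct only when the residual variances are equal across visits. Under equal SDs and AR(1) correlation of 0.6 to 0.8 per 4 weeks, the error is moderate: the test is conservative at week 4 and has a type I error of roughly 6.5% to 9% at week 12. Under exchangeability there is no error, and under falling variance the direction reverses. These sizes rest on assumed correlations and complete data. The point is a worthwhile, inexpensive improvement and does not show that the primary analysis is invalid. The case for the change does not depend on the direction, because visit-specific variances remove the problem either way and cost almost nothing where there is none.

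**What to change.** In Statistical analysis, replace the random-intercept description for VD and HD with a repeated-measures model:

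- Responses are weeks 4, 8 and 12; baseline enters only as a covariate.
- The within-participant covariance is unstructured, with visit-specific variances.
- Fixed effects are group, visit, group-by-visit, baseline and baseline-by-visit, plus the two allocation factors from Study design and methods (age ≤50 or >50 years; onset ≤30 or >30 days).
- State a small-sample degrees-of-freedom method that can be combined with Rubin's rules over the 20 imputed datasets.
- Name a simpler covariance structure to use if the model does not converge.

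FMA-UE and MBI follow automatically, since they use the same approach.

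**Cost.** This changes wording only, with no extra data or visits. Three visits need 3 × 4 / 2 = 6 covariance parameters instead of 2, a negligible loss of precision with 60 participants.
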